## 1.3 Adverse Events after brain re-irradiation

Adverse events (AEs) in ReRT retrospective studies are often poorly registered and therefore underestimated. Most larger retrospective studies do not report severe acute toxicity or radionecrosis at all [9, 10, 14, 15]. Only few studies, including one phase-I prospective study, reported severe acute toxicity [23, 24]. Some studies reported high rates of radionecrosis, including 30% radionecrosis in the SRT group of the retrospective study of

Cho et al. [25], 36% reported late adverse events in the prospective study by Shepherd et al. [26] and 43% in the minority of patients that were progression-free 10 weeks after treatment in the prospective study of Moller et al. [23]. In the pooled results of a meta-analysis on ReRT in glioblastoma, grade  $\geq 3$  toxicity rates were poorly reported, but considered to be 4-10%, with higher rates in prospective studies [20]. Real difference in toxicity could be assigned to differences in radiotherapy prescription and patient characteristics. However, the large variation among studies is probably for the most part caused by insufficient detection in retrospective studies. It is of great importance to accurately record and analyze AEs after ReRT to assess safety and its influence on HRQoL.

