#### 6.1.3 Other study parameters

In addition, KPS will be recorded in the experimental arm 1 and molecular analysis on prior surgically acquired tumor tissue, as well as at the time of recurrence (if available), will be performed.

### 6.2 Study procedures Arm 1

After obtaining informed consent (for details, see section 9.2), patients will receive treatment and necessary follow-up procedures. During the course of the study, participating centers will collect baseline characteristics, technical data such as MRI's, CT's and treatment plans and date of death. Medical imaging will be uploaded to a radiological database at a FTP server. Central data collection exists of HRQoL assessment, toxicity, anti-edema therapy and performance status. Central data collection will be performed by the study team by phone call, or via digital or paper questionnaires. Study procedures are summarized in Table 3. Patients will complete HRQoL questionnaires and the study team will record toxicity and anti-edema treatment by phone call at baseline and at 2, 4, 6, 13, 26, 39, and 52 weeks from the start of ReRT or until disease progression (whichever is sooner). During the first 6 weeks HRQoL will be assessed using the EQ-5D-5L. At subsequent time points QLQ-C15-PAL and BN20+2 will be completed digitally or on paper. Clinicians will be asked to record toxicity, KPS and anti-edema therapy use during regularly scheduled consults.

In case of suspicion of progression, recurrence or radionecrosis on MRI without consensus of diagnosis by the tumor board a FDG-PET, FET-PET or spectroscopy may be used to differentiate but is not mandatory.

IDH-1/2 mutation and MGMT-methylation will be determined at baseline using prior surgically acquired tissue, when molecular analysis has not been performed before, as well as at the time of recurrence (if available).

Any clinical follow-up data after 12 months will be uploaded at time of death, if known.

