### **8.1.4 Toxicity**

Toxicity will only be assessed in the experimental group. Analyses of radiotherapy toxicity will be performed in all patients who received at least one fraction. Acute events occurring from start of radiotherapy until 90 days and late events occurring from 91 days after end of radiotherapy will be presented. Further analyses of treatment toxicity will present the grade 3 to 5 acute or late side effect by treatment arm. The time to occurrence of any severe late side effects and separately radionecrosis (distinguishing symptomatic and asymptomatic) will be estimated by cumulative incidence. The time to severe late side effects will be calculated from the time of start of radiation treatment to the first evidence of any grade 3-5 late side effects. Patients alive without grade 3-5 late toxicity will be censored at the date of last

follow-up, patients who died without experiencing late grade 3-5 side effects will be assessed as competing risk at the time of death.

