## **8.3 Interim analysis**

Six months after inclusion of every 10 patients an interim analysis will be performed to review the toxicity data. If the toxicity is unexpectedly high in large tumors (65-125cc), the maximal tumor diameter will be modified to 5 cm (reflecting a spherical tumor of 65 cc). The detailed interim analyses are not made available to trial participants.

Sequential boundaries will be used to monitor dose-limiting toxicity rate. Full follow-up for acute toxicity is defined as 90 days after last irradiation fraction. Full follow-up for radionecrosis is defined as after the MRI at 6 months. This is a Pocock-type stopping boundary that yields the probability of crossing the boundary at most 0.05 when the rate of dose-limiting toxicity is equal to the acceptable rate 30, 20 or 10% depending on adverse event grading [45].

The research team will be responsible for the interim analysis. The accrual of patients with a tumor with a diameter >5 cm will be halted if excessive numbers of dose-limiting toxicities are seen, that is, if the number of dose-limiting toxicities is equal to or exceeds  $b_n$  out of  $n$  patients with full follow-up (Table 4.1, 4.2 and 4.3). No more interim analyses will be performed if accrual of patients with a tumor volume of >5 cm (reflecting a spherical tumor of 65 cc) is halted based on the above, if after 4 iterations of interim analyses, no excessive numbers of dose-limiting toxicities are seen, as mentioned above or when inclusion is completed without excessive dose-limiting toxicities. In any of these cases, the METC that gave a favorable opinion will be notified.

**Table 4.1 The maximal tumor volume will be modified if the number of dose limiting grade 3 to 5 toxicities is equal to or exceeds  $b_n$  out of  $n$  patients with completed follow-up. This boundary is equivalent to testing the null hypothesis, after each patient, that the event rate is equal to 0.3, using a one-sided level 0.017041 test.**

|                         |    |    |    |    |    |    |    |    |    |    |    |    |    |    |    |    |    |    |    |    |
|-------------------------|----|----|----|----|----|----|----|----|----|----|----|----|----|----|----|----|----|----|----|----|
| Number of Patients, $n$ | 1  | 2  | 3  | 4  | 5  | 6  | 7  | 8  | 9  | 10 | 11 | 12 | 13 | 14 | 15 | 16 | 17 | 18 | 19 | 20 |
| Gr 3-5 Boundary, $b_n$  | -  | -  | -  | 4  | 5  | 5  | 6  | 6  | 7  | 7  | 8  | 8  | 9  | 9  | 10 | 10 | 10 | 11 | 11 | 12 |

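### Study-team toxicity calls stop at progression, but the late-toxicity analysis keeps progressed patients at risk, so late toxicity in arm 1 is likely to be under-ascertained

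*Protocol*

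**What the plan says.** **Collection (protocol section 6.2).** At baseline and weeks 2, 4, 6, 13, 26, 39 and 52, "the study team will record toxicity and anti-edema treatment by phone call". The schedule runs to week 52 "or until disease progression (whichever is sooner"). The stop applies to toxicity and anti-edema treatment as well as to the questionnaires.

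**Other sources (sections 6.2 and 7.2.1).**
- A second channel has no stated stop at progression: "Clinicians will be asked to record toxicity, KPS and anti-edema therapy use during regularly scheduled consults".
- Table 3 has information and imaging uploads at weeks 26 and 52.
- Later data are conditional: "Any clinical follow-up data after 12 months will be uploaded at time of death, if known".
- Adverse event reporting under section 7.2.1 closes 30 days after the last fraction, so it does not reach late toxicity.

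**Analysis (section 8.1.4).** Late events start 91 days after the end of radiotherapy. Time to severe late effects, and separately to radionecrosis, is estimated by cumulative incidence. "Patients alive without grade 3-5 late toxicity will be censored at the date of last" follow-up, and patients who die without the event are a competing risk at the date of death. Progression is not mentioned, and last follow-up is not tied to the last toxicity assessment.

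**The concern.** A cumulative incidence estimate assumes that an event in a patient still at risk would be seen. Consider a patient who progresses at month 3 and dies at month 9. The analysis counts that patient as free of late toxicity throughout, yet the study team made no toxicity call in the last six months. Any event in that time enters the data only if a clinician recorded it or an upload revealed it.

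The two rules meet in the late window. Of the scheduled calls, only those at weeks 26, 39 and 52 clearly fall in it, and many patients may have progressed before it opens.

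Late grade 3-5 toxicity and radionecrosis are central safety results for this re-irradiation schedule, and section 7.4 sets up no DSMB. Section 1.3 shows that the protocol knows detection depends on how data are collected. It says of the published rates that "the large variation among studies is probably for the most part caused by insufficient detection in retrospective studies". Toxicity that is not collected cannot be recovered at analysis.

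**Working it through.** The protocol gives no expected late-toxicity incidence for arm 1, so there is no planned figure to reproduce. The check asks how far the estimate could fall under stated assumptions.

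**Inputs from the protocol**
- 12-month mortality 0.7 (section 4.4), so 12-month survival is 0.30.
- Radionecrosis 5-14% in the literature (section 1.1), used as two assumed true 12-month incidences.
- 66 patients in arm 1.

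**Assumptions (not in the protocol)**
- Median PFS m = 3, 4 or 6 months, exponential.
- Death hazard before progression 0.02 per month.
- Constant late-toxicity hazard h from month 3.5, equal before and after progression.
- A share c of post-progression events reaches the data: 0, 50% or 90%.
- No other censoring before month 12.

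**Step 1. Hazards.** The PFS hazard is λ = ln 2 / m and the progression hazard is λ − 0.02. The post-progression death hazard μ solves

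exp(−12λ) + (λ − 0.02)·[exp(−12μ) − exp(−12λ)] / (λ − μ) = 0.30.

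For m = 4, λ = 0.173 and μ = 0.221: 0.125 + 0.153 × (0.0705 − 0.125)/(0.173 − 0.221) ≈ 0.125 + 0.175 = 0.30. For m = 3 and m = 6, μ is 0.167 and 0.592.

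**Step 2. State at month 3.5, when the late window opens.** The progression-free share is exp(−3.5λ). The share alive after progression, whose calls have stopped, comes from the second term in Step 1 with 3.5 in place of 12.

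| Median PFS (months) | Progression-free | Alive, calls stopped |
|---|---|---|
| 3 | 44.5% | 36.9% |
| 4 | 54.5% | 26.9% |
| 6 | 66.7% | 10.9% |

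**Step 3. Observed incidence.** Choose h so that the full 12-month incidence equals the assumed truth. Then observed = pre-progression events + c × post-progression events. For m = 4 and a true 14%, 7.6 points arise before progression and 6.4 after. At c = 0.5 the estimate is 7.6 + 0.5 × 6.4 = 10.8%.

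| True | Capture after progression | m = 3 | m = 4 | m = 6 |
|---|---|---|---|---|
| 14% | none | 5.2% | 7.6% | 11.8% |
| 14% | 50% | 9.6% | 10.8% | 12.9% |
| 14% | 90% | 13.1% | 13.4% | 13.8% |
| 5% | none | 1.8% | 2.7% | 4.2% |
| 5% | 50% | 3.4% | 3.8% | 4.6% |
| 5% | 90% | 4.7% | 4.8% | 4.9% |

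The observed share of the truth runs from 37% to 98%.

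**Step 4. Would changing the censoring rule alone help?** Moving censoring to the last toxicity assessment affects only patients who are alive. Those who die after progression, in a group with 70% mortality at 12 months, still count as event-free until death. Censoring everyone at progression estimates a different quantity: 8.0-8.4% for a true 5% and 22-23% for a true 14%.

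**Step 5. Cost of continuing the calls.** Extra calls = 66 × the sum, over weeks 13, 26, 39 and 52, of the probability of being alive after progression. For m = 4: 66 × (0.254 + 0.283 + 0.236 + 0.176) ≈ 63. For m = 3 it is about 85, and for m = 6 about 21.

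**The case against.** The strongest objection is that progressed patients are not unobserved. Section 6.2 asks clinicians in advance to record toxicity at scheduled consults, with no stop at progression, and uploads are planned at weeks 26 and 52. By the Appendix 2 definitions, grade 3-5 necrosis or seizure means severe symptoms, intervention, threat to life or death, and such events tend to reach the treating clinician. This stands. It means that the no-capture rows are a limit and not an estimate. The protocol's remark on detection is also about retrospective studies and does not transfer directly to a consented prospective arm.

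The size also matters. With 50% capture and a median PFS of 4 months, the shortfall on 14% is 3.2 points. The binomial standard error with 66 patients is √(0.14 × 0.86 / 66) = 4.3 points. This stands too, although the shortfall always runs in the reassuring direction and is not covered by the confidence interval.

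A reader might infer that the interim radionecrosis counts are truncated in the same way. Section 8.3 does not support this: "Full follow-up for radionecrosis is defined as after the MRI at 6 months". Nothing there makes that MRI, or the count, depend on the calls.

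Stopping calls at progression also fits the stated aim of limiting patient burden. That is a fair reason for the rule, but section 8.1.4 would then need to match it.

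**Conclusion.** The mismatch is in the text: structured recording stops at progression or week 52, and time at risk does not. Followed as written, the two rules push the late-toxicity and radionecrosis incidence downward unless capture through clinicians and uploads is complete.

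A reader might go further and say that late toxicity is definitely understated, or that a true 14% would be reported as 5%. The documents do not support that, because they leave open how complete the clinician channel is. What they support is that under-ascertainment is likely and its size unknown. The range in the working rests on the assumed median PFS, a toxicity hazard unaffected by progression, and the assumed capture shares.

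Toxicity is a secondary endpoint. Overall survival, the sample size and the non-inferiority decision are unaffected. This should be fixed, but it does not put the trial's main conclusion at risk.

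**What to change.** **Section 6.2.** Lift the progression stop for toxicity and anti-edema recording only, and continue those calls to week 52 or death. The questionnaire schedule can stay as it is.

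**Section 8.1.4.** Censor living event-free patients at their last toxicity assessment, and report cumulative incidence to 12 months only, since later data arrive at death and only if known.

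**If the calls must stop at progression.** Count progression as a competing event alongside death, and label the result as late toxicity before progression. This is coherent but answers a narrower question. Changing the censoring date without this step leaves deaths after progression unrepaired.

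**Cost.** A protocol amendment and roughly 20-85 short calls over the trial under the assumptions above; fewer if some of the 13 patients carried over from trial A are already past their call dates. There is some added burden for patients and families after progression. Attribution also becomes noisier once the tumor has progressed; the five-level scale in Appendix 2 gives a way to record that judgement but does not remove the uncertainty.

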### **8.1.5 Prognostic and predictive factors**

Additional exploratory analyses using Cox regression analyses will study the prognostic impact of factors (other than treatment, age, gender, WHO-grade primary tumor, time interval in between first radiation and re-irradiation and MGMT-status), including baseline KPS, number of recurrence, tumor volume and dexamethasone use at baseline. In addition, the predictive value for the treatment effect of the 4 and 10 fraction regimens of these factors will be investigated using Cox Regression analyses.

## **8.2 Other study parameters**

### **8.2.1 Demographic and baseline characteristics**

Data on demographic and baseline characteristics will be summarized using descriptive statistics. For continuous variables, in case of normal distribution by means and standard deviations, and in case of non-normal distribution by medians and interquartile ranges. For discrete variables data will be summarized by frequencies and proportions.

## **8.3 Interim analysis**

Six months after inclusion of every 10 patients an interim analysis will be performed to review the toxicity data. If the toxicity is unexpectedly high in large tumors (65-125cc), the maximal tumor diameter will be modified to 5 cm (reflecting a spherical tumor of 65 cc). The detailed interim analyses are not made available to trial participants.

Sequential boundaries will be used to monitor dose-limiting toxicity rate. Full follow-up for acute toxicity is defined as 90 days after last irradiation fraction. Full follow-up for radionecrosis is defined as after the MRI at 6 months. This is a Pocock-type stopping boundary that yields the probability of crossing the boundary at most 0.05 when the rate of dose-limiting toxicity is equal to the acceptable rate 30, 20 or 10% depending on adverse event grading [45].

The research team will be responsible for the interim analysis. The accrual of patients with a tumor with a diameter >5 cm will be halted if excessive numbers of dose-limiting toxicities are seen, that is, if the number of dose-limiting toxicities is equal to or exceeds  $b_n$  out of  $n$  patients with full follow-up (Table 4.1, 4.2 and 4.3). No more interim analyses will be performed if accrual of patients with a tumor volume of >5 cm (reflecting a spherical tumor of 65 cc) is halted based on the above, if after 4 iterations of interim analyses, no excessive numbers of dose-limiting toxicities are seen, as mentioned above or when inclusion is completed without excessive dose-limiting toxicities. In any of these cases, the METC that gave a favorable opinion will be notified.

**Table 4.1 The maximal tumor volume will be modified if the number of dose limiting grade 3 to 5 toxicities is equal to or exceeds  $b_n$  out of  $n$  patients with completed follow-up. This boundary is equivalent to testing the null hypothesis, after each patient, that the event rate is equal to 0.3, using a one-sided level 0.017041 test.**

|                         |    |    |    |    |    |    |    |    |    |    |    |    |    |    |    |    |    |    |    |    |
|-------------------------|----|----|----|----|----|----|----|----|----|----|----|----|----|----|----|----|----|----|----|----|
| Number of Patients, $n$ | 1  | 2  | 3  | 4  | 5  | 6  | 7  | 8  | 9  | 10 | 11 | 12 | 13 | 14 | 15 | 16 | 17 | 18 | 19 | 20 |
| Gr 3-5 Boundary, $b_n$  | -  | -  | -  | 4  | 5  | 5  | 6  | 6  | 7  | 7  | 8  | 8  | 9  | 9  | 10 | 10 | 10 | 11 | 11 | 12 |
| Number of Patients, $n$ | 21 | 22 | 23 | 24 | 25 | 26 | 27 | 28 | 29 | 30 | 31 | 32 | 33 | 34 | 35 | 36 | 37 | 38 | 39 | 40 |
| Gr 3-5 Boundary, $b_n$  | 12 | 13 | 13 | 13 | 14 | 14 | 15 | 15 | 15 | 16 | 16 | 16 | 17 | 17 | 18 | 18 | 18 | 19 | 19 | 20 |

**Table 4.2 The maximal tumor volume will be modified if the number of dose limiting grade 4 or 5 toxicities is equal to or exceeds  $b_n$  out of  $n$  patients with completed follow-up. This boundary is equivalent to testing the null hypothesis, after each patient, that the event rate is equal to 0.2, using a one-sided level 0.015124 test.**

|                         |    |    |    |    |    |    |    |    |    |    |    |    |    |    |    |    |    |    |    |    |
|-------------------------|----|----|----|----|----|----|----|----|----|----|----|----|----|----|----|----|----|----|----|----|
| Number of Patients, $n$ | 1  | 2  | 3  | 4  | 5  | 6  | 7  | 8  | 9  | 10 | 11 | 12 | 13 | 14 | 15 | 16 | 17 | 18 | 19 | 20 |
| Gr 4-5 Boundary, $b_n$  | -  | -  | 3  | 4  | 4  | 5  | 5  | 5  | 6  | 6  | 6  | 7  | 7  | 7  | 8  | 8  | 8  | 9  | 9  | 9  |
| Number of Patients, $n$ | 21 | 22 | 23 | 24 | 25 | 26 | 27 | 28 | 29 | 30 | 31 | 32 | 33 | 34 | 35 | 36 | 37 | 38 | 39 | 40 |
| Gr 4-5 Boundary, $b_n$  | 9  | 10 | 10 | 10 | 11 | 11 | 11 | 11 | 12 | 12 | 12 | 13 | 13 | 13 | 13 | 14 | 14 | 14 | 15 | 15 |

**Table 4.3 The maximal tumor volume will be modified if the number of dose limiting grade 5 toxicities is equal to or exceeds  $b_n$  out of  $n$  patients with completed follow-up. This boundary is equivalent to testing the null hypothesis, after each patient, that the event rate is equal to 0.1, using a one-sided level 0.015673 test.**

|                         |    |    |    |    |    |    |    |    |    |    |    |    |    |    |    |    |    |    |    |    |
|-------------------------|----|----|----|----|----|----|----|----|----|----|----|----|----|----|----|----|----|----|----|----|
| Number of Patients, $n$ | 1  | 2  | 3  | 4  | 5  | 6  | 7  | 8  | 9  | 10 | 11 | 12 | 13 | 14 | 15 | 16 | 17 | 18 | 19 | 20 |
| Gr 5 Boundary, $b_n$    | -  | 2  | 3  | 3  | 3  | 4  | 4  | 4  | 4  | 4  | 5  | 5  | 5  | 5  | 5  | 6  | 6  | 6  | 6  | 6  |
| Number of Patients, $n$ | 21 | 22 | 23 | 24 | 25 | 26 | 27 | 28 | 29 | 30 | 31 | 32 | 33 | 34 | 35 | 36 | 37 | 38 | 39 | 40 |
| Gr 5 Boundary, $b_n$    | 6  | 7  | 7  | 7  | 7  | 7  | 7  | 8  | 8  | 8  | 8  | 8  | 8  | 9  | 9  | 9  | 9  | 9  | 9  | 9  |

The most objective toxicity terms will be evaluated, including central nervous system necrosis, edema and seizures. Maximal accepted percentage grade 3 to 5 radiotherapy related acute toxicity or late radionecrosis (severe symptoms; medical intervention indicated) is 30%. Maximal accepted percentage grade 4 or 5 adverse events is 20%. Maximal accepted percentage grade 5 adverse events is 10%. Toxicity terms are graded according to the CTCAE v5.0 (Appendix 1.0). Edema will be graded similar to radionecrosis.

If maximal tumor diameter has to be modified to 5 cm, expected loss of recruitment amounts 15% based on the retrospective dataset of UMC Utrecht and UMC Groningen. The recruitment time should be prolonged with approximately 5 months to achieve a total of 65 patients.

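### Section 8.3 prints toxicity boundaries for a test after each patient but schedules at most four reviews, so the rule is more conservative and acts later than its construction intends

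*Protocol*

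**What the plan says.** Section 8.3 describes a Pocock-type boundary that "yields the probability of crossing the boundary at most 0.05" when the true rate of dose-limiting toxicity equals the acceptable rate: 30% for grade 3-5, 20% for grade 4-5 and 10% for grade 5. Tables 4.1 to 4.3 print a boundary b_n for every n from 1 to 40. The caption of Table 4.1 states: "This boundary is equivalent to testing the null hypothesis, after each patient, that the event rate is equal to 0.3". The captions of Tables 4.2 and 4.3 say the same for rates of 0.2 and 0.1.

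The review schedule in the same section is different: "Six months after inclusion of every 10 patients an interim analysis will be performed to review the toxicity data". Reviews end, among other reasons, "if after 4 iterations of interim analyses, no excessive numbers of dose-limiting toxicities are seen". A patient counts in n only after full follow-up, which for radionecrosis means the 6-month MRI. Crossing a boundary halts accrual of tumors with a diameter above 5 cm. Section 7.4 states that there is no DSMB.

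**The concern.** The construction (40 looks) and the use (at most four looks) do not match. A boundary built for 40 looks is set high at each n, because the permitted 0.05 is spread over all of them. Read only four times, it keeps the high thresholds but loses most of the chances to cross. At stake is how often, and how soon, the rule restricts tumor size when toxicity is truly excessive. It is the only quantitative toxicity boundary in the protocol, the research team applies it without a DSMB, and the protocol gives no operating characteristics for the four-look use.

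**Working it through.** **Inputs (section 8.3).** Limit rates p0 = 0.30, 0.20 and 0.10. Printed b_n at n = 10/20/30/40: 7/12/16/20 (Table 4.1), 6/9/12/15 (Table 4.2) and 4/6/8/9 (Table 4.3). Assumption: the four reviews fall at exactly these n, counting patients with full follow-up.

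**Method.** Let f_n(s) be the probability of s toxicities in n patients with no crossing so far.
- Step: f_n(s) = f_{n-1}(s)(1-p) + f_{n-1}(s-1)p.
- At a look, x_n is the sum of f_n(s) over s ≥ b_n, and those states are then removed.
- Crossing probability = Σ x_n.
- Expected number evaluated = Σ n·x_n + 40(1 - Σ x_n), so runs that never cross count as 40.

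**1. The plan's own figure.** With a look after every patient and p = p0, the printed tables give 0.0500, 0.0497 and 0.0496. The stated 0.05 is therefore the 40-look figure.

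**2. Four looks at p = p0.**
- Table 4.1: 0.0106 + 0.0032 + 0.0037 + 0.0028 = 0.0203
- Table 4.2: 0.0064 + 0.0077 + 0.0051 + 0.0031 = 0.0222 (terms rounded)
- Table 4.3: 0.0128 + 0.0072 + 0.0034 + 0.0079 = 0.0312 (terms rounded)

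A hand check for Table 4.1: the plain binomial tails at the four looks are 0.0106, 0.0051, 0.0064 and 0.0063. Their sum, 0.0284, is an upper bound on the crossing probability and is already well below 0.05.

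**3. Detection when toxicity is excessive.** The last column uses constant-level boundaries recalibrated to four looks, with a total of at most 0.05 per table: 7/11/15/18, 6/9/11/14 and 4/6/7/9. Their totals at p0 are 0.049, 0.039 and 0.041.

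| Table | True rate | Each patient | Four looks, printed b_n | Four looks, recalibrated |
|---|---|---|---|---|
| 4.1 | 40% | 0.295 | 0.186 | 0.353 |
| 4.1 | 45% | 0.513 | 0.383 | 0.597 |
| 4.1 | 50% | 0.730 | 0.620 | 0.807 |
| 4.1 | 60% | 0.965 | 0.939 | 0.984 |
| 4.2 | 30% | 0.352 | 0.260 | 0.365 |
| 4.2 | 40% | 0.799 | 0.734 | 0.826 |
| 4.3 | 20% | 0.500 | 0.456 | 0.497 |
| 4.3 | 30% | 0.916 | 0.904 | 0.916 |

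**4. Timing.** Expected number evaluated under Table 4.1: 24.4 versus 30.4 at a 50% rate, and 15.1 versus 21.3 at 60% (each patient versus four looks, printed b_n).

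**5. Dependence on the look sizes.** With all four looks 1 to 5 patients earlier, the crossing probability at p0 is 0.014-0.027 (Table 4.1), 0.015-0.029 (Table 4.2) and 0.017-0.026 (Table 4.3). All remain well under 0.05.

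**6. The three tables together.** Assume nested grades, one outcome per patient and all three rates at their limits: 70% none, and 10% each with grade 3, 4 or 5 as worst grade. The chance that at least one boundary is crossed is 0.107 with a look after each patient, 0.056 with four looks at the printed b_n, and 0.092 with the recalibrated boundaries.

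**Side observation.** Tables 4.2 and 4.3 match their captioned levels at every n. Table 4.1 is one event higher than its captioned level of 0.017041 implies at n = 15, 22, 27, 30, 35 and 40. The printed values correspond to a level of about 0.014, and a strict 0.017041 boundary tested after each patient would cross with probability 0.057.

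**The case against.** A reader might infer that the rule breaks its stated error limit, or that it is less than half as likely to fire as stated. Neither holds in general. The protocol promises a crossing probability of at most 0.05, and 0.020, 0.022 and 0.031 all satisfy that. Relative to the 40-look value, the ratios are 41% and 45% for Tables 4.1 and 4.2 but 63% for Table 4.3, and all three shift with the number of evaluable patients at each look.

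The sensitivity loss is also uneven. It is 11 to 13 points for grade 3-5 at rates of 40-50%, 6 to 9 points for grade 4-5 at 30-40%, and 1 to 4 points for grade 5 at 20-30%. At very high rates the rule fires almost surely either way.

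Nor does a later crossing mean that many more patients are exposed. The action restricts only tumors above 5 cm, and section 8.3 puts the recruitment lost by that at 15%. If this is their share of accrual, a gap of 6 evaluated patients is about 6 × 0.15 = 0.9 large-tumor patients, leaving aside those enrolled during the follow-up lag.

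Other safeguards exist. Section 6.2 collects toxicity by phone at seven time points after the start of re-irradiation, section 7.2.2 requires expedited SAE reporting, and section 7.1 obliges the sponsor to suspend the study if safety is jeopardized.

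These points limit the size of the problem. They do not remove the contradiction between captions and schedule, and none of the other safeguards is a quantitative boundary. The recalibrated column also shows that four looks need not cost detection: apart from 0.3 of a point for grade 5 at 20%, it equals or exceeds testing after each patient. The loss in detection comes from using 40-look thresholds at four looks. Some delay from batching would remain.

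**Conclusion.** The concern holds as an internal contradiction that makes the safety rule needlessly conservative, not as a breach of a stated error limit. With looks at 10, 20, 30 and 40 patients with full follow-up, the crossing probability at the limit rate is about 0.02, 0.02 and 0.03 per table instead of 0.05. Detection falls by up to about 13 points for grade 3-5, less for grade 4-5 and little for grade 5, and action comes about 6 evaluated patients later at grade 3-5 rates of 50-60%.

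The exact figures rest on the assumed look sizes and on n counting all patients with full follow-up. Section 8.3 does not say clearly whether n covers everyone or only large tumors; in the second case n at each look would be far smaller and the printed figures would not apply. This is a moderate point that is cheap to repair.

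**What to change.** Reconcile the captions and the schedule in section 8.3. There are two consistent options, and the choice is the sponsor's:

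- Compare the running count with the printed b_n each time a patient completes follow-up, and keep the report per 10 patients as a summary.
- Keep at most four reviews and recalibrate all three tables to the looks actually planned. The boundaries in the working illustrate this for looks at 10, 20, 30 and 40.

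In either case, state whether n counts all patients or only those with large tumors, check the captioned level of Table 4.1 against its entries, and report the operating characteristics per table and for the three tables jointly.

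The editing cost is a few sentences, plus either a running tally by the team that already reviews the data or three short recalculated tables. The statistical cost is more false restriction at the limit rates. It stays within 0.05 per table, but jointly, under the nested-grade assumption above, it rises from about 0.056 to about 0.09 (recalibrated) or 0.11 (each patient). The sponsor should accept that figure knowingly or set a joint limit.
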